## Introduction

### Background and rationale

Epilepsy is one of the most common chronic neurological conditions worldwide, imposing a high burden of disease on people affected and on society [1]. In Germany, around 500,000 people are affected by epilepsy [2]. An accurate diagnosis of epilepsy and other seizure disorders, such as psychogenic non-epileptic seizures or syncopes, is crucial to avoid misdiagnoses and to create a correct treatment plan, leading to an improved quality of life (QoL) for people affected and preventing fatal seizures [3].

Therefore, equipping healthcare systems with the right tools to make a timely diagnosis is important to avoid a lack of healthcare services, especially in rural areas [4]. The current gold standard for diagnosing epilepsy and other seizure disorders is an inpatient long-term video-electroencephalogram (EEG) monitoring (VEM). However, inpatient monitoring is only available at limited specialized centers and is associated with significant time and work resources [5]. Further, there are still fewer neurologists and pediatric neurologists in the rural eastern parts of Germany, reflected by a higher number of epilepsy patients per neurologist, leading to a significant waiting time for inpatient long-term video EEGs [6]. To address these challenges, outpatient long-term video EEGs (ALVEEGs) have already been established in other countries [7]. The development of a new portable sensor technology, enhanced by innovative automated data analyses supported by artificial intelligence (AI), allows ALVEEGs in the patient’s home environment. This advancement facilitates faster and more accurate diagnoses in this setting. By aligning with the treatment gold standard of care, it helps preventing misdiagnoses and inappropriate treatment plans, thereby improving QoL of people affected by epilepsy and other seizure disorders [8].

As shown in a single-center feasibility study in Germany, ALVEEGs were well accepted by patients and clinicians. They may offer an equivalent way of diagnosing epilepsy and other seizure disorders in Germany [8].

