### Study outcomes

The outcomes of the study refer to the healthcare system (macro level), the institutional level (meso level) as well as the individual patient (micro level).

The primary outcome of ALVEEG is the proportion of clinical questions being solved in the IG compared to the CG. A clinical question is considered as solved if (1) a specified diagnosis is needed and provided via long-term video EEG, (2) treatment management needs to be defined and is provided via long-term video EEG, or (3) a specified diagnosis is needed, and treatment management needs to be defined according to findings of the long-term video EEG.

Secondary outcomes (see Table 1), include on the macro level: (1) number of hospital stays, (2) length of hospital stays, (3) inability to work (in days), and (4) number of video EEGs; on the meso level: (5) duration of waiting period for a video EEG (in days), (6) duration of waiting period for diagnosis and result discussion, (7) duration of diagnosis identification using AI, and (8) duration of long-term video EEG; and on the micro level: (9) number of diagnosis specifications, definition of treatment management and diagnosis specifications combined with treatment management, (10) number and form of epilepsy-related events and epileptiform activity, (11) QoL related to epilepsy, (12) QoL, (13) health status, (14) health competence, and (15) contentment, acceptance, and AE.

**Table 1 Tab1:** Secondary outcomes, time points, and measurement instruments

Outcome	Timepoint	Measurement Instrument
Number of diagnosis specifications, treatment management, diagnosis specification & treatment management (IC-CG)	tP1	Study data base
Number and type of epilepsy-related events or epileptiform activity (ictal, interictal, only video as quality indicator) *(IC-CG)*	*tD2*	Study data base
Waiting time for video EEG *(IC-CG)*	*t0-tSens*	Study data base
Duration until discussion of diagnosis/results *(IC-CG)*	*t0-tP1*	Study data base
Epilepsy-related quality of life *(IC-CG)*	*t0,tP2*	QOLIE-1 (PROM) via tablet, study data base
Quality of life *(IC-CG)*	*t0,tP2*	EQ-5D-5L (PROM) via tablet, study data base
Health status *(IC-CG)*	*t0,tP2*	EQ-5D-5L VAS (PROM) via tablet, study data base
Health competence/seizure awareness *(IC-CG)*	*t0,tP2*	Subscale PESOS (PROM) via tablet, study data base

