*t0 *at baseline*, tD2 *after diagnosis compilation by the neurologist*, tP1 *appointment to discuss medical findings (patient and neurologist)*, tP2 *3-month follow up appointment (patient and neurologist)*, tSens *time point of sensor/electrodes placement

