### Participant timeline

Randomization of patients into either the IG or CG will take place in the participating epilepsy centers at baseline (*t0*), after patients have given their informed consent. The treating neurologist will be informed about the patient’s group assignment, and all included patients are asked to complete REDCap (Research Electronic Data Capture) surveys on PROMs (IG and CG: EQ-5D-5L, EQ-5D-5L (VAS), as well as the QOLIE-10 and a subscale of the PESOS questionnaire). All questionnaires will be saved and managed in REDCap electronic data capture tools, hosted at the University of Nebraska Medical Center. REDCap is a secure, web-based application designed to support data capture for research studies [13, 14].

After randomization, patients will receive either inpatient (CG) or outpatient (IG) long-term VEM, with patients in the IG being trained in how to use ALVEEG (*tSens*). They can also call at any time if problems occur during the monitoring at home (*tMon1-tMon2*), and there will be a check-in on the first day of ALVEEG, led by a medical-technical assistant (MTA). Secondary outcome data will be assessed for both IG and CG throughout the study at different assessment time points (see Fig. 1). After the ALVEEG is completed (*tMon2*), patients in the IG will return the equipment to the hospital (*tEA*). The ALVEEG data will be uploaded into the cloud provided by the medical device company and documented in REDCap (*tAP*). The patient’s practitioner will also get access to the monitoring results, which are evaluated by the neurologist for patients in the IG and CG (*tD2*). After the evaluation of the monitoring is completed, the neurologist will discuss the results and care and treatment plan with the patient in both IG and CG (*tP1*). Patients will additionally answer a survey on their acceptance, contentment, and AE during ALVEEG. The follow-up assessment will take place three months after the discussion of medical findings, with patients in both groups answering the PROM questions in REDCap again (*tP2*).

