### Statistical methods: sample size, recruitment and power calculations

The sample size calculation for the presented equivalence trial is based on the primary endpoint. After consultation with the clinical consortium partners, the proportion of resolved clinical cases in the CG is assumed to be 0.8 (80%). We expect to observe an equivalent rate of treatment successes in the IG, whereby (clinical) equivalence is defined within a margin of +/- 15% deviation from the rate in the CG. This corresponds to an equivalence interval of [0.68–0.92] ([68 − 92%]) for the proportion of clinical questions being solved. This margin is based on assumptions made by clinical experts within the consortium and is further supported by the results of international studies on the subject [15].

Based on a significance level of 0.05 and a power of (1-β) = 90%, applying two proportions z-test results in a sample size of 482 participants. Considering an expected dropout rate of about 30%, the sample size of the study amounts to 688 participants. In order to achieve this sample, an average of approximately five patients must be recruited per center and month.

For the secondary endpoints, a power of 0.83 was computed using a two-sided t-test for 550 patients, taking into account the latency period of the routine data from the participating health insurance funds.

According to estimations by the consortium partners and the involved health insurance companies, it is assumed that the aspired sample size can be achieved for all endpoints.

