### Statistical methods

The primary analysis has the aim to evaluate the effect of ALVEEG based on the predefined primary endpoint, the proportion of cases being solved by the video EEG. Two one-sided z-tests will be performed, and a confidence interval will be determined based on the observed difference between IG and CG and interpreted using the predefined equivalence interval, analyzing the proportion of clinical questions being solved in the IG compared to the CG [17]. Point estimates of the intervention effect, together with the corresponding 95% confidence intervals, will be reported on the absolute and relative scale.

For the planned descriptive statistical analyses, mean values (standard deviation) for continuous normally distributed data, medians and interquartile ranges for non-normally distributed continuous data, and the proportions of frequencies for categorical data will be presented.

Depending on the relevant variables, various statistical test procedures and multivariable techniques will be applied in the context of secondary and sensitivity analyses to test the hypotheses within the context of inferential statistics. In principle, the inferential data analyses focus on differences between the IG and CG. For example, to test the difference in duration in days (e.g., waiting time until video EEG or length of in-hospital stay), we will perform a t-test for normal distributions or the Wilcoxson rank sum test for non-normally distributed data.

The entire statistical data analysis will be performed using the statistical software *R* [18] *v4.2.1* (or higher).

Prior to data lock and the actual extraction of the data, a detailed statistical analysis plan, including additional information on ancillary analyses and the handling of missing data, will be developed.

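### The t-test or Wilcoxon test named for waiting time has no place for randomised patients who never reach the video EEG, so the comparison may be biased in either direction

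*Protocol article*

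**What the plan says.** The protocol article, under Statistical methods, gives as its example of the secondary analyses that "to test the difference in duration in days (e.g., waiting time until video EEG or length of in-hospital stay), we will perform a t-test" when the data are normal, with a Wilcoxon rank sum test otherwise.

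Table 1 (Study outcomes) measures the wait for the video EEG over t0-tSens and the time to discussion of results over t0-tP1. The table legend defines tSens as "time point of sensor/electrodes placement". Under Participant timeline, "Randomization of patients into either the IG or CG will take place in the participating epilepsy centers at baseline", which is t0. Both clocks therefore start at randomisation and stop at an event that a randomised patient may not reach.

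On loss of patients, the sample size section says: "Considering an expected dropout rate of about 30%, the sample size of the study amounts to 688 participants". It does not say when the loss occurs, in which arm, or why. The background section describes a shortage of neurologists in rural eastern Germany "leading to a significant waiting time for inpatient long-term video EEGs", which is the control pathway. No wait in days is given for either arm.

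Handling of missing data and ancillary analyses are deferred to a statistical analysis plan to be written before data lock. The Discussion promises strategies for missing values by endpoint.

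**The concern.** A t-test or an ordinary rank sum test needs a completed duration for each patient. Someone who withdraws on day 90 without an EEG is known to have waited more than 90 days, but has no value to enter. The same holds for a late entrant still waiting when the data close. If such patients are left out, the comparison is conditional on reaching the EEG. That is a post-randomisation event whose probability may differ between the arms, since patients know their allocation and the inpatient queue is expected to be longer.

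Faster access is one of the project's stated hopes, so waiting time is likely to be read closely even though it is a secondary outcome. Time to results discussion has the same structure and, by extension, the same problem.

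**Working it through.** **1. The plan's own figures.** With a rate of 0.80 in both arms, a margin of 15% of 0.80 = 0.12, two one-sided tests at 0.05 and 90% power:

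n per arm = 2 × 0.8 × 0.2 × (1.645 + 1.645)² / 0.12² = 240.5, so 241 per arm and 482 in total, as stated. Then 482 / 0.70 = 688.6, against 688 stated. The 30% is thus a genuine planning figure: 0.30 × 688 ≈ 206 patients. How many of them would be lost before the EEG is unknown.

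**2. One case by hand.** All waits are assumptions. Let waits be exponential with mean W and let loss while waiting have a constant hazard m, equal in both arms. Then:

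- observed mean among those who reach the EEG = W / (1 + mW)
- share lost before the EEG = mW / (1 + mW)

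Take W = 120 days (control) and 45 days (intervention), a true difference of 75 days.

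- m = 1/180 per day: control 120 / (1 + 0.667) = 72 days with 40% lost; intervention 45 / (1 + 0.25) = 36 days with 20% lost. Average loss is 30%. Observed difference 36 days, and 36/75 = 0.48.
- m = 0.00221 per day: control 120 / 1.265 = 94.8 days; intervention 45 / 1.099 = 40.9 days. Average loss is 15%. Observed difference 53.9 days, and 53.9/75 = 0.72.

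**3. Other shapes and mechanisms.** A simulation with 400,000 patients per arm used gamma waits with assumed means (intervention/control) of 30/90, 60/90 and 60/120 days. Shape 1 is the exponential; higher shapes are less dispersed. The table gives the difference among those who reached the EEG as a share of the true difference.

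| Loss mechanism | Wait shape | Share retained |
|---|---|---|
| Same hazard while waiting in both arms, 30% lost before EEG | 1 / 2 / 4 | 0.48-0.49 / 0.69-0.70 / 0.83 |
| Same hazard, 15% lost before EEG | 1 / 2 / 4 | 0.72 / 0.85 / 0.92 |
| Data closed at last recruitment, no other loss | 2 | 0.87-0.92 |
| Data closed 180 days later, no other loss | 2 | 0.94-0.98 |
| Loss unrelated to the wait, 30/30% or 15/45% (intervention/control) | 2 | 1.00 |
| Wait-related loss in the intervention group only (hazard 0.006 per day, 16-28% lost) | 2 | 1.04-1.31 |

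The result depends on whether loss is tied to time waited, and in which arm. The overall dropout rate does not settle it: loss of 15% against 45% gives no bias when it is unrelated to waiting.

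**The case against.** The strongest reply is that the protocol never restricts this analysis to patients with an EEG date. It defers missing-data handling to the analysis plan, promises strategies for missing values, and offers the test only as an example beside unspecified multivariable and sensitivity analyses. A rank test can also include patients without an EEG by giving them the worst rank. All of this is correct, so a reader should not infer that the named tests can use only patients who reached the EEG. What remains is that the protocol does name the test for this outcome, that the deferral covers missing data rather than the choice of test, and that in standard form the test discards the information in an incomplete wait.

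A reader might also infer that long waits will drop out and that the benefit is therefore underestimated. The documents do not support this. They do not link dropout to waiting, and some of the 30% may be lost after electrode placement, before results discussion or follow-up. The fall from 75 to 36 days puts all 30% before the EEG and uses the most dispersed wait shape, so it lies at the unfavourable end.

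Loss through early data closure is not established either. Recruitment ends in June 2026, results are due in 2027, and each patient has a visit three months after the results discussion. With closure 180 days after last recruitment, little is lost.

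Finally, a bias toward zero would shrink a claimed benefit rather than create one. That holds only for the mechanism that is similar in both arms.

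**Conclusion.** The point stands as a weakness of the method named for a secondary outcome. A comparison limited to patients who reached the EEG may be biased, and neither the direction nor the size can be known from the protocol. Under assumed waits and 15-30% loss before the EEG, about 48-92% of the true difference is retained if loss rises with time waited similarly in both arms and the control wait is longer. The bias is nil if loss is unrelated to waiting. Its direction reverses, to 104-131% of the true difference, if wait-related loss occurs only in the intervention group. Every magnitude rests on assumed waits and loss patterns.

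It would go too far to say that the waiting-time benefit will be underestimated. The primary equivalence test and its sample size are untouched. The change is recommended rather than essential.

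**What to change.** In the analysis plan, analyse t0-tSens and t0-tP1 in all randomised patients as time-to-event from randomisation:

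- **Main analysis:** Kaplan-Meier curves by arm with withdrawal censored, a centre-stratified log-rank test, and the difference in restricted mean waiting days, to a horizon fixed in advance, with 95% confidence interval.
- **Sensitivity analysis:** cumulative incidence of reaching the event, with withdrawal as a competing event.
- **Reporting:** number and share lost before tSens, by arm.

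The main analysis relies on non-informative censoring. The constant-hazard and data-closure mechanisms in the working meet that condition, because the time of loss does not depend on the remaining wait. Real withdrawals may not, hence the sensitivity analysis.

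The cost is analysis-plan wording, standard R code and a recorded withdrawal date. The summary is less familiar than a mean among those who reached the EEG. No sample size or primary analysis changes.

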### Evaluation of the implementation of ALVEEG

To evaluate the implementation of ALVEEG, its delivery, further implementation and its generalizability, we will use the RE-AIM framework [19]. The RE-AIM framework facilitates assessing the benefits of innovative forms of care, while taking into account their successful implementation [20].

Therefore, the number of approached patients compared to those actually participating is measured to assess whether the intervention reaches the intended target population (REACH). The number of achieved treatment successes will also be recorded and evaluated accordingly (EFFECTIVENESS). In addition, we will examine the extent to which the included study sites participated in the intervention (ADOPTION) and the implementation of intervention activities according to protocol (IMPLEMENTATION). Furthermore, we will investigate the degree to which the intervention can be sustainably integrated into routine processes (MAINTENANCE).

### Health economic evaluation

A health economic evaluation will be carried out alongside the trial, investigating whether the intervention is cost effective compared to standard care. The evaluation will be performed from a statutory health insurance perspective and will comprise a cost-utility as well as additional cost-effectiveness analyses. The outcome to be considered for the cost-utility analysis will be quality-adjusted life years (QALYs), calculated by data obtained from the EQ-5D-5L questionnaire under applying German population weights [21].

Additional emerging costs with relevance to the intervention will be considered compared to standard care (e.g., ALVEEG devices, staff education, etc.), as well as costs per patient stemming from health insurance data (e.g., number of hospitalizations, medications, travel expenses, etc.).

## Discussion

The shortage of inpatient VEM capacities for patients with epilepsy and other seizure disorders in Germany, in addition to the artificial environment of VEMs taking place in hospitals instead of the patient’s usual surroundings, requires better care and access for this population - especially in rural areas, where resources and neurological specialists are limited. As shown in previous studies from other countries, ALVEEGs allow a faster and more effective diagnosis and management of epilepsy and other seizure disorders [7, 8].

We expect that results from this study will deliver insightful evidence on the effectiveness of ALVEEGs in diagnosis and management of epilepsy and other seizure disorders compared to the current inpatient gold standard - not only on the patient and clinical level but also with respect to the German statutory health care system. Further, we will be able to provide a more nuanced understanding of the intervention and its impact, as well as cost-utility and cost-effectiveness results, as we are evaluating different endpoints, while taking into account multiple outcomes and intervention-associated costs.

Nevertheless, there are some limitations to our study. As we collect data from a real-world clinical care setting, we expect missing data to occur, especially when it comes to self-reported information. Being aware of this, we will address this issue through the elaboration of statistical strategies to account for missing values for the different endpoints to be assessed. Further, as blinding of the treating neurologist and data analyst is not possible due to the nature of the trial design, potential bias cannot be ruled out. However, we do not expect any major impact, i.e., bias on the effects to be analyzed.

Finally, claims data from German statutory health insurances are subject to a waiting period for up to 9 months. Therefore, it will not be possible to analyze claims data from all included patients. Further, we will only be able to analyze claims data for patients who are part of the participating three statutory health insurances: BARMER, DAK-Gesundheit and TK. Although in total there are 96 statutory health insurances in Germany, the insurance companies participating in this trial are part of the biggest German statutory health insurances [22]. Hence, we believe that patients for whom claims data will be available are representative of the entire ALVEEG study population.

One major strength of the study is its pragmatic nature, allowing to generate real-world evidence on the use of ALVEEGs in clinical care processes as a new diagnostic pathway in epilepsy centers in Germany. Although we do not expect any possible harm for participating patients, we made sure that potentially occurring AE during the trial will be continuously monitored and patients will have access to professional support throughout the trial.

The evaluation of this study will provide valuable information for decision makers to optimize future delivery of neurological care to patients affected by epilepsy and other seizure disorders, and to guide a possible scale-up of ALVEEGs in Germany. Further, conducting an implementation and health economic evaluation alongside this trial will provide essential information for key stakeholders in the German healthcare system.

### Trial status

Patient recruitment started in April 2024. In June 2026, the last patient will be recruited. Results are expected in 2027.

## Data Availability

No datasets were generated or analyzed during the current study.

## Abbreviations

AE: Adverse events
AI: Artificial intelligence
ALVEEGs: Outpatient long-term video EEG
CG: Control group
ECG: Electrocardiogram
EEG: Electroencephalogram
EQ-5D-5L: European quality of life questionnaire – 5 dimensions
G-BA: German Innovations Fund of the Federal Joint Committee
ICER: Incremental cost-effectiveness ratio
IG: Intervention group
MTA: Medical-technical assistant
OPS: Operation and procedure classification system
PESOS: Performance, Socio-demographic aspects, Subjective evaluation Fragebogen
PROMs: Patient reported outcome measures
QALYs: Quality-adjusted life years
QoL: Quality of life
QOLIE-10: Quality of life in epilepsy
RCT: Randomized controlled trial
REDCap: Research Electronic Data Capture
TK: Techniker Krankenkasse
VAS: Visual analogue scale
VEM: Video-EEG monitoring
